### Theory of change and implementation science framework

This study is guided by a Theory of Change and the Practical, Robust Implementation and Sustainability Model.

#### Theory of change (ToC)

A ToC can be used to guide the planning, implementation, and evaluation of public health programs in low-resource settings and provides a comprehensive illustration of how and why a desired change is expected to happen in a particular context [10, 11]. In the phase 1 study, a rigorous, multi-step process was used with the CSAB to create a ToC [6] that will be confirmed and used to inform implementation and evaluation planning. This ToC illustrates the root causes, conditions needed, and measures of success to mitigate disparities in COVID-19 testing access and care.

#### Practical, robust implementation and sustainability model (PRISM)

PRISM will guide the optimization, implementation, and evaluation of the study’s multi-component implementation strategy bundle [12–14]. PRISM allows for multi-level conceptualization of implementation efforts (context domains) and provides guidance on how to measure relevant implementation outcomes through integration of the RE-AIM measures (Reach, Effectiveness, Adoption, Implementation, Maintenance)—one of the most widely used set of implementation measures [15]. PRISM is ideal for guiding real-world community-based research because it accounts for multi-level effects, it builds on several implementation science frameworks, and it can guide development, implementation, and evaluation. PRISM will be used to consider multiple levels of context, recipient characteristics (community members and promotores, conceptualized as delivery agents), intervention characteristics (as perceived by diverse partners), implementation and sustainability infrastructure within communities and clinics, and the external environment (national guidelines and regulations regarding COVID-19 testing and management). In addition to effectiveness, the study will assess the RE-AIM outcomes of reach, adoption, implementation, and maintenance.

### Aims

The specific aims of the study are as follows:

#### Aim 1

To refine and operationalize a multi-component implementation strategy bundle and a related set of outcome metrics for COVID-19 testing.

#### Aim 2

To implement and evaluate the impact of the innovative, multilevel, and multicomponent implementation strategy bundle to optimize COVID-19 rapid testing among underserved communities in Central and South San Diego using a roll-out implementation optimization study design across 4 clinics over 18 months.

## Methods

### Study design

The multi-component COVID-19 testing implementation strategy bundle and outcome metrics will be operationalized and refined using a participatory approach engaging diverse community, clinic, and research partners through a CSAB, brainwriting premortem interviews [16] and the PRISM Fit Assessment (Aim 1). The implementation strategy bundle to optimize COVID-19 testing among underserved communities will be tested using a roll-out implementation optimization (ROIO) study design [17] (Aim 2). See Fig. 1 for the study design and timeline.

**Fig. 1 Fig1:**
[figure not shown]
CO-CREATE-Ex participatory (Aim 1) and ROIO (Aim 2) design and timeline

The primary outcome is defined as offering the most clinically useful COVID-19 test and returning results within an optimal timeframe to enable appropriate treatment and decrease transmission, in the most acceptable, timely, and feasible manner. Secondary outcomes include increased: reach to priority communities; adoption and meaningful, sustained implementation of the testing strategy bundle; optimal COVID-19 testing experiences; and metrics that matter most to clinical and community partners such as rates of preventive care engagement. The ROIO study design allows for iterative refinement of the implementation strategies after each clinic roll-out [17]. Longitudinal data mixed-methods data collection and analysis with multiple partners and community members will inform necessary refinements and assessment of the impact of the strategy bundle on key outcomes over time.

### Setting

This study will be conducted in partnership with a high-performing FQHC that serves low-income and uninsured San Diegans and has a long-standing relationship with the lead university. For this study, we will focus on clinics in Central and South San Diego. As shown in Table 1, the 4 target clinics serve primarily Latino and Black patients, and a large proportion report Spanish as their primary language. Preventive healthcare rates for commonly recommended adult preventive screenings and immunizations are low, particularly for blood pressure (*M* = 60.6% across clinics) and flu immunization (*M* = 20.4% across clinics) [18].

**Table 1 Tab1:** FQHC clinic characteristics

	Clinic 1	Clinic 2	Clinic 3	Clinic 4
Total # patients	18,124	20,102	8328	8120
Patient race/ethnicity				
Latino	91.6%	79.0%	61.2%	74.3%
Black	1.3%	3.0%	16.9%	12.1%
Asian	1.5%	4.7%	4.7%	2.2%
White	14.4%	15.0%	29.4%	15.3%
Patient preferred language				
Spanish	70.1%	56.7%	36.0%	48.8%
Adult preventive health services (% of “active” patients who completed a medical visit and had a preventive health service in the past 18 months)				
Blood pressure screening	55.4%	62.3%	58.2%	66.3%
HbA1c screening	78.9%	79.3%	72.8%	81.6%
Flu immunization	25.0%	15.5%	16.2%	24.9%
COVID-19 cases/100,000 (2/20–4/22)	48,219	31,623	34,209	35,716
RATs distributed since 1/22	785 (*M* = 196/month)	499 (*M* = 125/month)	244 (*M* = 61/month)	192 (*M* = 48/month)

### Participants

Recruitment of community members will occur at the FQHC clinics through collaborative efforts between promotores, and on-site research staff. Recruitment and outreach will occur on-site for patients coming to the clinic for appointments, through outreach at local community gathering locations, phone calls, and/or emails to existing FQHC patients, outreach by CSAB members utilizing their existing networks, social media posts, flyers, and/or billboards. It is anticipated that participants will represent the ethnic, racial, and sex distributions of the registered patients at each participating clinic. Promotores will be hired by the partnering FQHC and speak the languages that are most common in the local communities and clinics (Spanish and English).

### Community and scientific advisory board (CSAB)

Building on the phase 1 CSAB, a slightly modified membership for the current study’s CSAB will facilitate representation from communities around the 4 participating clinics for the Aim 2 implementation and evaluation activities. In addition to 4 community partners, the CSAB will include 2–3 clinical staff, 1–2 public health researchers, 1–2 policy partners, and a County Public Health Department ambassador. CSAB community partners will be selected based on their role as community weavers—that is, individuals with lived experience as a member of an underserved community who are cultural brokers between communities, health systems, and researchers to co-create community-driven public health solutions.

### Aim 1 procedures

To refine and operationalize the implementation strategy bundle and measures of implementation and sustainment success, several participatory methods will be used. During CSAB meetings led by the Global ARC, initial strategies, measures, and data collection plans will be presented. The research team will facilitate group brainwriting premortem interviews [16] with the CSAB to gather information about what specific components of the implementation strategy bundle and measurement might be prone to fail and to co-create solutions to prevent these failures.

#### Data collection and analysis

Aim 1 data collection will focus on evaluating the quality, extent, and content of partner engagement through the participatory CSAB activities. An established multimethod ethnographic approach [19] using a refined documentation form will be completed by trained research interns at each CSAB meeting, and a partner engagement survey based on validated measure from Goodman and colleagues [20] will be completed by all CSAB attendees after each session. Data from the partner engagement survey will be analyzed after each CSAB meeting to inform post-meeting debriefings with the Global ARC and research team. Aim 1 data (brainwriting premortem interviews, ethnographic documentation forms, engagement surveys) will be analyzed using a rapid qualitative analytic approach and simple descriptive statistics. Summarized data from these sources will be triangulate using a joint display analysis [21, 22]. This methodology has been described in more detail in Rabin et al. [19]. In addition, the research team will document adaptations made to the implementation strategies throughout the Aim 1 refinement process (and throughout Aim 2) using methods developed by Rabin et al. and that was used in the phase 1 study [19, 23].

### Aim 2 procedures

An innovative ROIO study design [17] will be used to implement and evaluate the multilevel, and multicomponent implementation strategy bundle (Fig. 1). Four cycles of preparation, initial roll-out (3 months), and sustainment will be launched over 21 months. Refinements to the implementation strategy bundle and processes will be made prior to each new roll-out based on information collected from the prior roll-out (or the CSAB preparation for Clinic 1) and a PRISM Fit Assessment. The PRISM Fit Assessment will explore how well the proposed strategy bundle aligns with the multi-level context of Clinic 1, how likely the proposed bundle will lead to increased rapid COVID-19 testing, reach of community members, and adoption and sustained implementation. The PRISM Fit Assessment will be repeated prior to each subsequent clinic roll-out. Each PRISM Fit assessment will involve clinic staff, promotores, and clinic operational leaders completing a 21-item survey developed around the key PRISM context domains and related RE-AIM outcomes independently followed by a group review of the summary results to discuss any misalignments and additional needs for refinement in the context of the specific clinic. This process will be repeated for each clinic prior to roll-out and at the end of the study period.

Preparation phases last 3 months and include data collection from patients/community members, clinic providers/staff, and promotores, medical assistant, and onsite testing staff, rapid analysis of this information and triangulation with other testing information, presentation to and refinement with the CSAB, and finalization based on PRISM Fit Assessment data. During the initial roll-out phase (3 months), the full-intensity implementation strategy bundle is provided at the clinic. After 3 months, clinics move into continued services with vending machines and promotores, available on an as-needed basis. Walk-up testing will also decrease in intensity moving to a setup with one part-time staff operating the walk-up testing.

#### Data collection

Quantitative and qualitative data will be collected using multiple databases and methods. Data collection methods are summarized in Table 2 with the data source name, type of data collected, origin of data and timing for data collection, and associated PRISM domains assessed. Data from the PRISM Fit Assessment will be summarized as descriptive statistics and displayed in the form of bar graphs to inform the group action planning discussion. Key implementation and clinical and public health effectiveness outcomes are summarized in Table 3. The timing for each data collection method is also noted in Fig. 1. Participants will be required to provide contact information and minimum symptom and exposure data prior to obtaining rapid tests and the type of test and timing of testing will be captured for both the walk-up onsite testing and vending machine testing along with basic demographics. Participants will also be invited to provide rapid test results and receive personalized health counseling based on their test result.

**Table 2 Tab2:** Data sources, data types, origin and PRISM domains

Data source name	Type	Origin/timing	PRISM domains
REDCap study database for rapid COVID-19 testing (QUAL + QUANT)	Database completed by walk-up onsite testing staff about number of tests completed, reason and timing for testing including symptoms and exposure, community member demographics	Walk-up onsite testing staff Ongoing	Reach Implementation Maintenance
Preventive care status and health characteristics (QUANT)	Electronic health records data on primary and secondary outcomes, participant demographics, other health characteristics	SYH Research Assistant accessing electronic health records After each initial roll-out	Reach Recipient characteristics Effectiveness
Promotore support activities database (QUAL + QUANT)	# of days and hours promotore services are provided; # and type of support activities	Promotores Ongoing	Adoption Implementation Maintenance
Vending machine automatic data log (QUANT)	#, timing, type of interactions with vending machine; reason and timing for testing, type of test used; participant demographics	Programmed in vending machine Ongoing	Reach Effectiveness Implementation Maintenance
Periodic reflections with promotores, medical assistant, and onsite testing staff (QUAL)	Key lessons learned, facilitators, challenges of implementation of the testing strategy bundle	Promotore FQHC Research Assistant Other onsite testing staff After each initial roll-out	Intervention characteristics Implementation and sustainability infrastructure External environment
Community member interviews (QUAL)	Experience with the multicomponent implementation strategy for testing at each clinic	Subset of participants (*n* = 60, 15/clinic) After each initial roll-out	Implementation Effectiveness Maintenance
FQHC provider and staff interviews (QUAL)	Experience with the multicomponent implementation strategy for testing at each clinic	Subset of providers and staff (*n* = 12, 3/clinic) After each initial roll-out	Recipient characteristics Adoption
PRISM Fit Assessment (QUAL + QUANT)	Fit of proposed strategy bundle with multilevel PRISM context domains and RE-AIM outcomes with clinic operational leaders, providers and staff, and promotores	Clinic operational leaders, providers and staff, promotores Before each roll-out and at the end of the study period	All PRISM context and RE-AIM outcomes
Adaptation documentation database (QUAL + QUANT)	Ongoing documentation of adaptations occurring in Aim 1 and Aim 2 to implementation strategies and procedures	UCSD clinical research staff Ongoing	Implementation

**Table 3 Tab3:** Implementation and effectiveness outcomes

Implementation outcomes	Reach	The absolute number, proportion, and representativeness of community members who attend the walk-up onsite testing; interact with the promotores for support; and/or utilize the vending machines compared to all eligible community members on key characteristics. Reasons for non-participation
	Adoption	Demographic and professional characteristics of promotores (adoption staff level) and characteristics of clinics (adoption site level)
	Implementation	# of days and hours walk-up onsite testing is delivered, # of staff at testing, # of test completed at walk-up onsite testing, # of days and hours promotores delivering support per clinic and the type of support delivered, # of days and hours vending machines operate at clinic site and types of services provided through the machine, number of tests dispensed through the vending machines
	Maintenance	Ongoing operation of walk-up onsite testing beyond initial roll-out at Clinic 1; ongoing promotore services provided beyond initial roll-out (first 3 months) at all clinics (and type of support); ongoing operation of vending machines beyond initial roll-out (first 3 months)
Effectiveness (clinical and public health) outcomes	COVID-19 RAT completion	Number of RATs distributed through the walk-up onsite testing and vending machines
	Optimal COVID-19 testing experience	Offering the most clinically useful COVID-19 test and returning results within an optimal timeframe to enable appropriate treatment and decrease transmission, in the most acceptable, timely, and feasible manner
	Preventive care engagement	Up-to-date age/sex-specific preventive care (e.g., flu shot; cancer screening) based on participants’ demographic and health characteristics

Qualitative interviews with patients/community members and clinic providers/staff will be conducted after each initial roll-out period (after 3 months of implementation) to understand their experiences with the implementation strategy bundle and identify potential areas for improvement. A total of 60 interviews with patients/community members evenly recruited from each of the 4 clinics will be conducted. Patients/community members will be identified for interviews based on their interest expressed when initially obtaining tests as part of the walk-in onsite clinic or vending machine. An additional set of interviews will be conducted with 12 providers/staff (3/clinic) identified based on their involvement in supporting the implementation or having exposure to the implementation strategy bundle.

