### Implementation strategies

The current study will refine and test three implementation strategies for optimal COVID-19 testing (evidence-based practice): (1) walk-up no-cost testing, (2) Community Health Worker (Promotores)-facilitated testing and preventive care counseling, (3) vending machines that dispense no-cost, self-testing kits. These strategies were prioritized by the CSAB of the phase 1 study using implementation mapping [9].

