#### Walk-up no-cost testing protocol

A no-appointment, walk-up point-of-care rapid testing at the partnering FQHC will continue at clinic 1 based on the success of the phase 1 study. Testing will be offered several times per week and titrated to lower intensity following the first clinic rollout. Trained, bilingual staff will oversee the on-site testing protocol. The walk-up testing protocol will not be offered at the other clinic sites.

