#### Data analysis

Quantitative data from study databases will be summarized using simple descriptive statistics including frequencies, measures of central tendency, and variability along with data visualization methods, such as frequency tables, bar charts, line graphs, and scatter plots to understand patterns and characteristics of testing uptake, exposures, and symptoms and to guide adaptive implementation. Missingness in data will be examined via sensitivity analysis and imputation methods will be applied when appropriate. Parametric and non-parametric tests will be employed to compare the survey responses between the clinics while controlling for a variety of demographic and socioeconomic variables, including the FQHC clinic cluster. Data collected at the point of test distribution (collected by study coordinators, promotores, and vending machines) will be used to evaluate implementation strategy effectiveness on testing uptake. Hierarchical multilevel models will be used to ensure the inclusion of random effects, variation between clusters, variation between times within clusters, and the fixed effect of time which will be estimated independently of treatment effect so that systematic change over time will not be mistaken for effect of treatment. This is key, based on significant variations in testing uptake observed during previous COVID-19 variant waves. To account for potential within-clinic correlation, data will be reduced for each cluster to a single observation, and then subject to standard two-sample analyses. Secondary analyses will be conducted to determine the appropriateness of the test type distribution within the context of symptom onset and exposure time frame.

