### Power size calculations

The number of participating clusters/clinics and target clinic participant enrollment for the ROIO study design was determined using cluster randomized trial sample size estimation tools. Per the ROIO study design, each clinic cluster will begin in the control group and then cross over into the intervention group at different time points and then continue with the intervention until the end of the study (see Fig. 2). Although it is anticipated that the implementation strategies as outlined by CSAB will undergo some adjustments during the implementation process, the target cluster/clinic sample size estimates are based on a stepped wedge design using serial cross-sectional evaluations of electronic medical records and test kits distributed. It is estimated that the study will have the capacity to distribute 52,000 FDA-authorized rapid antigen tests provided by the San Diego County Health and Human Services and the California Department of Public Health. The primary outcome is the increased distribution of RATs within the communities near each of the 4 clinics. This will be measured using a proxy outcome defined as the proportion of clinic patients visits to the number of RAT kits distributed per month at each participating clinic. Currently, RAT kit distribution among target clinic patients ranges from 7 to 13% (*M* = 9%) with approximately 430 kits being distributed per month between all four clinics. The aim is to increase distribution of test kits to 40% of clinic patient encounters per month, which would result in the distribution of 1822 kits per month during the final treatment sequence. Based on data collected from the phase 1 study, approximately 40% of testing uptake occurred among clinic patients and the remaining 60% from community members even when the intervention was clinic-based. It is anticipated that there will be a similar community uptake during this study. Based on the sequential rollout outlined in the Fig. 2 with rollout for Clinic 1 at month 4, Clinic 2 at month 8, Clinic 3 at month 12, and Clinic 4 at month 16, over the course of the entire study it is anticipated that a total distribution of 20,503 tests, assuming average distribution per clinic. Estimating that this will equal approximately 40% of total increase and the remaining uptake to occur among community members, a total uptake of 58,091 test kits is estimated over the course of the study. Using the Shiny CRT Calculator [24], it was determined that a minimum cluster sample size of 285 across 4 clinics will provide sufficient power (beta > 0.8) to determine an intervention proportion increase of 0.05 to 0.25 assuming the following: stepped-wedge design, cross-sectional sampling structure at each of 4 sequences (approximately every 3 months in the study), 0.5 coefficient of variation in cluster sizes (based on average number of patient encounters per month per clinic), intra-cluster correlation (ICC) of 0.02, for our binary outcome (test or no-test). It was also assumed that there will be an exchangeable cluster correlation structure as SARS-CoV-2 testing demand has been impacted significantly by changes in variant severity and transmissibility.

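### The kit outcome has two unreconciled definitions; under the study-channel one, control months at Clinics 2–4 are zero by construction and displaced routine kits count as gain

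*Protocol article*

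**What the plan says.** Three places in the protocol article define or feed the kit outcome.

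- **Table 3, COVID-19 RAT completion:** "Number of RATs distributed through the walk-up onsite testing and vending machines". Only two channels count.
- **Data analysis:** "Data collected at the point of test distribution (collected by study coordinators, promotores, and vending machines) will be used to evaluate implementation strategy effectiveness". No source for routine clinic handouts is named.
- **Power size calculations:** the outcome called primary there is increased RAT distribution. Its proxy relates kits distributed per month at each clinic to patient visits, with no limit on channel. The starting level is "approximately 430 kits being distributed per month between all four clinics", on average 9%.

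The design text decides which channels exist in control months. The power section says that "each clinic cluster will begin in the control group and then cross over into the intervention group at different time points". Vending machines are one of the three strategies under test. Walk-up testing "will continue at clinic 1 based on the success of the phase 1 study"; for the rest, "The walk-up testing protocol will not be offered at the other clinic sites". Table 1 shows that all four clinics were already giving out RATs: 196, 125, 61 and 48 a month.

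**The concern.** A before/after contrast needs the same measurement on both sides of the crossover. Under Table 3, Clinics 2–4 have no counted channel before roll-out: walk-up is never offered there, and the vending machine arrives with the bundle. The kits they already hand out would not be counted, but the same kits would be counted once they came from a machine. A change of channel would then look like an increase in distribution.

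Clinic 1 has a different problem. It is labelled control until month 4, yet one bundle component, which is also a counted channel, is already running. Its crossover adds promotores and vending to existing walk-up testing, whereas Clinics 2–4 start from neither study channel. The outcome and the contrast therefore mean different things across the four clinics.

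**Working it through.** **Inputs.** Table 1: 785, 499, 244 and 192 kits since January 2022, with stated monthly means of 196, 125, 61 and 48. Power section: roll-out at months 4, 8, 12 and 16; baseline 430 kits a month; target 40% of encounters, or 1,822 kits a month.

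**1. The plan's baseline.** 785/4 = 196.25, 499/4 = 124.75, 244/4 = 61 and 192/4 = 48, which sum to 430. The target implies 1,822/0.40 = 4,555 encounters a month, and 430/4,555 = 9.4%. Both figures reproduce, so the power-section baseline is the sum of Table 1's clinic counts. Clinics 2–4 supply 125 + 61 + 48 = 234 of the 430 (54%).

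**2. Control months without a counted channel.** Control months are 3, 7, 11 and 15, total 36. Clinics 2–4 have 7 + 11 + 15 = 33. Routine kits left out at Table 1 rates: 124.75×7 + 61×11 + 48×15 = 873 + 671 + 720 = 2,264.

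**3. Pure substitution, no true gain.** All routine kits move to the vending machine at roll-out.

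| Clinic | All-channel change per month | Table 3 change per month |
|---|---|---|
| 2 | 0 | +125 |
| 3 | 0 | +61 |
| 4 | 0 | +48 |
| Sum | 0 | +234 |

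**4. Do period effects remove it?** Take four clinics and five periods, one clinic crossing over per step, and fit clinic, period and treatment effects by least squares to noise-free means. The treatment estimate is then a weighted mean of the clinic-specific changes, with weights 0.2, 0.3, 0.3 and 0.2 for Clinics 1–4. With Clinic 1 at 196 throughout (change 0), Table 3 gives 0.3×125 + 0.3×61 + 0.2×48 = +65.4 kits per clinic-month, against a true 0. A monthly grid gives +66 (21 months) to +68 (18 months). Period effects do not remove it.

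**5. At the planned effect.** Scale each clinic by 1,822/430 = 4.24, and suppose that all kits after roll-out pass through counted channels.

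- All-channel changes: 634.5, 404.7, 197.5 and 155.4, sum 1,392. Weighted estimate 338.6.
- Table 3 changes: 634.5, 529.7, 258.5 and 203.4, sum 1,626. Weighted estimate 404.0.
- Inflation: 1,626/1,392 = 1.17, and 404.0/338.6 = 1.19.
- On the proportion scale, the contrast at Clinics 2–4 is 0 to 0.40 instead of 0.094 to 0.40, and 0.40/0.306 = 1.31.

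**6. Range.** On the kit scale the error equals the routine kits displaced into study channels. If a share s is displaced, the summed error is 234×s and the model error is 65.4×s. With s = 0 (routine handout continues unchanged beside the machine) the kit difference is unbiased, although the control level is still zero. With s = 1 the figures in steps 3 to 5 apply.

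**The case against.** The strongest reply is that the power section governs. Its proxy has no channel limit and a non-zero baseline that matches Table 1, and Table 3 is presented only as a summary of key outcomes. Table 2 also has an electronic health record source for primary and secondary outcomes, assigned to Effectiveness, and the power section refers to serial evaluations of medical records and kits distributed. This stands in part: it would be wrong to infer that the trial's contrast is shown to be biased, or that every data source is one of the bundle's own channels. But the article nowhere says that routine kits are captured in the health record, and it does not say which definition supplies the analysed count.

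No sentence states that vending machines are absent at Clinics 2–4 before roll-out, and the two design figures are not available here. It remains the natural reading, because a clinic already dispensing from a study machine would not be in control.

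The Limitations text discloses that one clinic hosted phase 1 and plans clinic-level covariates. That is a fair disclosure, but a covariate does not say what the crossover at Clinic 1 estimates.

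A reader might also infer that Clinic 1 is already past the 40% target. Phase 1 ran 24,422/24 = 1,018 tests a month; if Clinic 1 is the 13% clinic, its encounters are 196.25/0.13 = 1,510, and 1,018/1,510 = 67%. The documents do not support this. The type of phase 1 test is not given, nor is it shown that the volume persists. The power section attributes only about 40% of phase 1 uptake to clinic patients, so the like-for-like figure would be 407/1,510 = 27%, below the target.

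**Conclusion.** The point holds as a conflict between two outcome definitions with a conditional bias. If the Table 3 and Data analysis count is the one analysed, 33 of 36 control clinic-months are zero by construction. The effect at Clinics 2–4 is then overstated by up to 234 kits a month in total, or about 17–19% of the planned effect in steps 4 and 5, under full displacement of routine handouts. If the power-section proxy is analysed with all routine kits captured, this bias does not arise.

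The result assumes that no study machine runs before roll-out, that Table 1 rates continue through the control months, and that Clinic 1's 196 kits are fully counted throughout. The error at Clinic 1 runs the other way, as dilution. Its size, and hence the net error over four clinics, cannot be computed because no walk-up RAT volume before roll-out is given.

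**What to change.** - Use one outcome in Table 3, Data analysis and the power section: all RAT kits distributed per clinic-month by any channel (routine, walk-up, vending, promotores), in control and intervention months alike.
- Name the source of routine kit counts, such as the counts behind Table 1, and secure it for the control months before analysis.
- Keep the walk-up and vending counts as an implementation measure, where Table 3 already lists tests completed and tests dispensed.
- State that at Clinic 1 the control-to-intervention contrast is promotores plus vending on top of existing walk-up testing.
- While editing Table 3, rename the row as distribution, since it counts kits given out and not tests completed. This is a minor wording point.

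The cost is a wording change and continued use of clinic counts that evidently already exist. The downside is that an all-channel increase will look smaller than a study-channel count wherever routine handouts are displaced.
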